#### Secondary Performance End Points

The secondary end points are (1) plasma levels of inflammatory markers: interleukin (IL)-10, IL-1β, soluble IL-2 receptor, IL-6, IL-8, and tumor necrosis factor α before and immediately after transplantation and at 6, 12, 24, 48, and 72 hours after transplantation and C-reactive protein and white blood cells before and immediately after transplantation and at day 1, 2, and 3 after transplantation; (2) infiltrates and oedema measured by chest x-ray or CT scan of the thorax at day 1, 2, and 3 after transplantation; (3) highest daily arterial blood gas measurements recorded on day 1, 2, and 3 after transplantation, as a measure of lung function; (4) PGD severity as evaluated per standard clinical procedures using a rating scale from 0 to 3 on day 1, 2, and 3 after transplantation, as a measure of lung function; (5) presence of any grade of PGD on day 1, 2, and 3 after transplantation, as a measure of lung function; (6) total dose of norepinephrine administered in the first 72 hours; (7) mortality up to 48 months after transplantation; (8) lung diffusion capacity, measured by carbon monoxide diffusion, at 6, 12, 24, and 48 months after transplantation, as a measure of lung function; (9) forced expiratory volume, forced vital capacity, and total lung capacity measured by spirometry at 1, 3, 6, 12, 24, and 48 months after transplantation, as a measure of lung function; (10) occurrence of any acute rejection episodes (clinically treated and/or biopsy verified) up to 48 months after transplantation, as a measure of lung function; (11) chest CT findings at 1, 3, 6, 12, 24, 36, and 48 months after transplantation; (12) the presence of any CLAD and CLAD subtypes up to 48 months after transplantation, as a measure of lung function; (13) kidney function evaluated by measurement of serum creatinine levels; calculated glomerular filtration rate and need for renal replacement therapy on day 1, 2, and 3 and at 1, 3, 6, 9, 12, 24, and 48 months after transplantation; urea levels on day 1, 2, and 3 after transplantation; and iohexol-clearance at 3, 6, 9, 12, 24, 36, and 48 months after transplantation; and (14) QOL evaluated by the 36-Item Short Form Health Survey at 24 and 48 months after transplantation.

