#### Exploratory End Points

The exploratory end points are the collection of a portion of routinely collected transplanted lung tissue by transbronchial biopsy and bronchoalveolar lavage fluid (at least at 1, 3, and 12 mo, with additional time points if clinically indicated), collection of explanted recipient lung tissue, and collection of blood samples (at least before transplantation; immediately after transplantation; 6, 12, 24, 48, and 72 h; 1 and 2 wk; and 1, 3, 6, 9, 12, 24, 36, and 48 mo after transplantation, with additional time points if clinically indicated) in a biobank for future exploratory analyses. Sample collection protocols will be detailed in a separate standard operating procedure.

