### Methodology

#### Medical Chart Review

The following data will be collected from medical charts at specified timepoints: background variables (demographics, comorbidities, therapies, and perioperative data), FiO_2_ measurements (baseline and 0-72 h after transplantation, adjusted for ventilation), arterial blood gas measurements (baseline and d 1-3 after transplantation), radiological assessments (infiltrates and edema at d 1-3), PGD severity (d 1-3 using a 0-3 scale), total norepinephrine dosage (first 72 h), lung carbon monoxide diffusion capacity (baseline, 6, 12, 24, and 48 mo), spirometry (forced expiratory volume, forced vital capacity, total lung capacity at 1, 3, 6, 12, 24, and 48 mo), chest CT findings (1, 3, 6, 12, 24, 36, and 48 mo), CLAD assessment (presence and subtype up to 48 mo), renal function (serum creatinine, glomerular filtration rate, need for renal replacement therapy at specified intervals), urea levels (d 1-3), iohexol clearance (3, 6, 9, 12, 24, 36, and 48 mo), mortality data (up to 48 mo), acute rejection episodes (occurrence and type up to 48 mo), immunosuppressant levels (first 72 h), adverse events, and SAEs.

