#### Clinical Assessment

Data from assessments and visits will be obtained from the medical records. All data must be supported by the patient’s medical records, that is, source documentation, and subsequently stored in an electronic case record form (eCRF).

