#### Blinding

The physicians, perfusionists, and nurses administering the treatment will not be blinded. Thus, unblinding for these parties is not possible. Outcome assessors for long-term follow-up visits after 1 month will be blinded. Statisticians carrying out the analyses after the end of this study will be blinded. In the case of termination of the clinical investigation, the statisticians will only be unblinded after all analyses are complete, regardless of whether this study is terminated on time or prematurely.

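### Acute rejection counts a treatment decision and a histological finding as the same event, in an unmasked trial, and no separate histology result is specified alongside it

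*Protocol article*

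**What the plan says.** Under Secondary Performance End Points, item 10 is the "occurrence of any acute rejection episodes (clinically treated and/or biopsy verified) up to 48 months after transplantation". Either limb is enough.

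Medical Chart Review lists "acute rejection episodes (occurrence and type up to 48 mo" among the chart items, without defining type. Clinical Assessment adds: "Data from assessments and visits will be obtained from the medical records".

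On masking, Study Design and Setting states that the control group receives no comparator device. Blinding states: "The physicians, perfusionists, and nurses administering the treatment will not be blinded". The same section states: "Outcome assessors for long-term follow-up visits after 1 month will be blinded".

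Exploratory End Points describes the "collection of a portion of routinely collected transplanted lung tissue" for a biobank, obtained "by transbronchial biopsy and bronchoalveolar lavage fluid (at least at 1, 3, and 12 mo, with additional time points if clinically indicated". The article gives no fixed biopsy time after 12 months.

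**The concern.** Starting rejection treatment is a clinical judgement. If clinicians know the arm and expect it to matter, the threshold for that judgement can differ between arms, and item 10 records the difference as a difference in rejection. The Discussion makes such expectations plausible: it suggests that filtration may support graft acceptance, and it reports histopathological rejection in untreated but not in treated feasibility patients.

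At stake is the reading of one of 14 secondary end points. With the composite alone, a difference between arms could reflect fewer rejections or fewer decisions to treat, and a reader could not tell which.

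**Working it through.** **The passages side by side**

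1. The definition joins its two limbs with and/or, so treatment without tissue meets it.
2. Unblinding is stated for staff administering the device, which is used for 12 hours within the first 24 hours after surgery. The article does not say whether clinicians who decide on rejection treatment weeks or months later know the arm. No blinding of them, or of the chart, is described.
3. Assessor blinding starts after 1 month, so earlier episodes have no stated blinded assessment.
4. After 1 month the blinded assessor takes the event from the record. For a treated-only episode, the event is the treating clinician's decision, and reading it blind does not change it.
5. Routine biopsies at 1, 3 and 12 months are fixed in time and so do not depend on clinical suspicion. Additional biopsies are taken when clinically indicated, so verified rejection on any biopsy also depends partly on clinicians' decisions.

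**Illustration of size**

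The protocol states no figure for acute rejection, so there is none to reproduce. The only input from the document is 58 patients per arm (Sample Size). The rates below are assumptions.

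- b = proportion with biopsy-verified rejection, the same in both arms (no true effect): 20% or 30%.
- c = proportion of the remaining patients treated without histology, which may differ by arm.
- Observed proportion per arm: p = b + (1 − b) × c.
- Standard error of the difference: SE = √[p₁(1 − p₁)/58 + p₂(1 − p₂)/58].
- Two-sided false-positive rate at .05, with δ = (p₁ − p₂)/SE: Φ(−1.96 + δ) + Φ(−1.96 − δ).

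Worked case, b = 20% and c = 15% versus 5%:

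- p₁ = 0.20 + 0.80 × 0.15 = 0.32
- p₂ = 0.20 + 0.80 × 0.05 = 0.24
- SE = √(0.32 × 0.68/58 + 0.24 × 0.76/58) = 0.083
- δ = 0.08/0.083 = 0.96
- False-positive rate = 0.160 + 0.002, about 16%

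| Verified, both arms | Treated-only, one arm vs the other | Observed end point | Odds ratio | False-positive rate |
|---|---|---|---|---|
| 20% | equal | equal | 1.00 | 5% |
| 20% | 10% vs 5% | 28% vs 24% | 1.23 | about 8% |
| 20% | 15% vs 5% | 32% vs 24% | 1.49 | about 16% |
| 30% | 10% vs 5% | 37% vs 33.5% | 1.17 | about 7% |
| 30% | 15% vs 5% | 40.5% vs 33.5% | 1.35 | about 12% |

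The calculation is symmetric. If the arm with more treated-only episodes is the filtration arm, the error rates are the same and the false difference goes against filtration.

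**The case against.** - **Knowledge of the arm is not documented for the relevant clinicians.** A reader might infer that everyone who decides on rejection treatment is known to be unblinded. The Blinding section states this only for staff administering the treatment. Knowledge of the arm among later clinicians is a reasonable inference, not a stated fact. This stands, and the point is worded accordingly.
- **The direction is not settled.** A reader might infer that the bias must favour filtration. However, immunosuppressant plasma levels are a safety end point, and a clinician worried about low drug exposure under filtration could treat filtered patients more readily. This stands.
- **The size is assumed.** The 12-16% range needs a threefold difference in treated-only episodes. The milder case gives 7-8%, and equal rates give no inflation. The figures show what differential treatment would do, not that it will happen.
- **The composite is a legitimate choice.** It captures clinically important episodes without tissue. A reader might infer that scheduled-biopsy rejection should replace it as the lead definition. That version would leave out months 12 to 48 (36 of the 48) and episodes treated between biopsies. Earlier treatment could also alter the histology at the next scheduled biopsy, so it is not wholly free of treatment decisions. This stands, and the composite should stay.
- **A split may already be planned.** The chart item on type might separate the two limbs, and the full investigation plan and analysis plan are not shown. This cannot be excluded. The point therefore concerns the definition the article fixes. If the split is already in those documents, the fix is a matter of confirming it.

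**Conclusion.** The concern holds in a limited form. Item 10 lets a treatment decision alone count as rejection, in a trial with no sham device and no stated blinding of the clinicians who decide, and blinded chart reading after 1 month does not remove the resulting risk. A difference between arms in the composite is therefore not, on its own, evidence of a difference in rejection.

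The documents support neither a direction nor a size for the bias. The illustrative 7-16% false-positive range rests on assumed rates of verified and treated-only rejection, a two-sided test at .05 and complete data on 58 patients per arm. The primary end point, the sample size and the interim analysis are not touched. This is a worthwhile, low-cost improvement to one secondary end point and not a threat to the trial's main conclusion.

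**What to change.** Keep the composite to 48 months as defined. Pre-specify three outcomes alongside it:

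- (a) biopsy-verified rejection on the routine 1, 3 and 12 month biopsies, taken from pathology reports with no allocation on the referral;
- (b) biopsy-verified rejection on any biopsy, including clinically indicated ones;
- (c) treated episodes without histology.

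Add an eCRF field that separates these event types, and state whether clinicians who diagnose rejection know the arm. State in advance that a composite difference will be interpreted as an effect on rejection only if the histology result points the same way.

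The cost is end-point wording and one eCRF field. No additional biopsies are needed and clinical management does not change. The downside is small: the histology-only outcome on scheduled biopsies has fewer events and lower precision, covers only the first 12 months, and can be affected by earlier treatment. The change should be made before any unblinded results are seen, because afterwards it would be post hoc.

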#### Safety End Points

The safety end points are adverse events, serious adverse events (SAEs), and plasma levels of immunosuppressant drugs (cyclosporine, tacrolimus, everolimus, or sirolimus) in the first 72 hours after transplantation.

#### Exploratory End Points

The exploratory end points are the collection of a portion of routinely collected transplanted lung tissue by transbronchial biopsy and bronchoalveolar lavage fluid (at least at 1, 3, and 12 mo, with additional time points if clinically indicated), collection of explanted recipient lung tissue, and collection of blood samples (at least before transplantation; immediately after transplantation; 6, 12, 24, 48, and 72 h; 1 and 2 wk; and 1, 3, 6, 9, 12, 24, 36, and 48 mo after transplantation, with additional time points if clinically indicated) in a biobank for future exploratory analyses. Sample collection protocols will be detailed in a separate standard operating procedure.

### Methodology

#### Medical Chart Review

The following data will be collected from medical charts at specified timepoints: background variables (demographics, comorbidities, therapies, and perioperative data), FiO_2_ measurements (baseline and 0-72 h after transplantation, adjusted for ventilation), arterial blood gas measurements (baseline and d 1-3 after transplantation), radiological assessments (infiltrates and edema at d 1-3), PGD severity (d 1-3 using a 0-3 scale), total norepinephrine dosage (first 72 h), lung carbon monoxide diffusion capacity (baseline, 6, 12, 24, and 48 mo), spirometry (forced expiratory volume, forced vital capacity, total lung capacity at 1, 3, 6, 12, 24, and 48 mo), chest CT findings (1, 3, 6, 12, 24, 36, and 48 mo), CLAD assessment (presence and subtype up to 48 mo), renal function (serum creatinine, glomerular filtration rate, need for renal replacement therapy at specified intervals), urea levels (d 1-3), iohexol clearance (3, 6, 9, 12, 24, 36, and 48 mo), mortality data (up to 48 mo), acute rejection episodes (occurrence and type up to 48 mo), immunosuppressant levels (first 72 h), adverse events, and SAEs.

#### Follow-Up Questionnaires

QOL will be evaluated at 24 and 48 months after transplantation by designated follow-up assessors who are trained in the administration of the questionnaire. QOL scores will be collected using the Short Form Health Survey questionnaire, which assesses QOL and severity of disease for various chronic conditions [19].

#### Clinical Assessment

Data from assessments and visits will be obtained from the medical records. All data must be supported by the patient’s medical records, that is, source documentation, and subsequently stored in an electronic case record form (eCRF).

#### Safety Assessment

The investigators will report all SAEs and device deficiencies to the sponsor no later than 3 calendar days after they become aware of the event. The sponsor will report to the Swedish Medical Products Agency all of the following reportable events: (1) any SAE that has a causal relationship with the investigational device, the comparator or the investigation procedure, or where such causal relationship is reasonably possible; (2) any device deficiency that might have led to a SAE if appropriate action had not been taken, intervention had not occurred, or circumstances had been less fortunate; and (3) any new findings in relation to any event referred to above. Foreseeable adverse events related to LTx will not be reported [20-26].

#### Data Safety Monitoring Board

Safety reviews and oversight will be under the direction of a Data Safety Monitoring Board (DSMB). The DSMB will be composed of a statistician and 2 physicians (with knowledge in the therapeutic area) who otherwise are not involved in the clinical investigation and are independent from the sponsor, without any competing interests. The DSMB shall be blinded in their safety assessments but can request to unblind the analysis in case of safety concerns. The DSMB will also carry out the interim analysis of the primary outcome variable described in the statistical analysis section. The clinical investigation can be terminated if the DSMB determines that the number of adverse events in the intervention group is unacceptable.

#### Blinding

The physicians, perfusionists, and nurses administering the treatment will not be blinded. Thus, unblinding for these parties is not possible. Outcome assessors for long-term follow-up visits after 1 month will be blinded. Statisticians carrying out the analyses after the end of this study will be blinded. In the case of termination of the clinical investigation, the statisticians will only be unblinded after all analyses are complete, regardless of whether this study is terminated on time or prematurely.

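### Blinded outcome assessment is stated only for visits after 1 month, so PGD grade, any PGD and chest infiltrates on days 1-3 have no stated blinded assessment

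*Protocol article*

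**What the plan says.** The Blinding section of the protocol article sets out who is blinded:

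- Bedside staff: "The physicians, perfusionists, and nurses administering the treatment will not be blinded".
- Outcome assessors: "Outcome assessors for long-term follow-up visits after 1 month will be blinded".
- Statisticians: "Statisticians carrying out the analyses after the end of this study will be blinded". The section on statistical design adds that the groups are labelled A and B during the initial analysis.

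The Data Safety Monitoring Board section blinds the board's safety reviews, with an option to unblind.

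Under Secondary Performance End Points, three items fall before any blinded assessment begins:

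- End point 2: "infiltrates and oedema measured by chest x-ray or CT scan of the thorax at day 1, 2, and 3 after transplantation".
- End point 4: "PGD severity as evaluated per standard clinical procedures using a rating scale from 0 to 3 on day 1, 2, and 3 after transplantation".
- End point 5: "presence of any grade of PGD on day 1, 2, and 3 after transplantation".

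The Introduction defines PGD as a PaO2/FiO2 ratio below 300 together with radiographic infiltrates, citing an international guideline. The Medical Chart Review and Clinical Assessment sections take these data from the medical records.

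**The concern.** The Introduction places the onset of PGD in the first 72 hours. The stated blinded assessment begins only after that window has closed. PGD incidence and severity are named in the purpose of the trial, and less PGD heads the Discussion's list of anticipated clinical benefits.

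One part of the PGD definition is a recorded ratio. The other is a judgement about an image, and the grade combines the two. In a unit where staff know who had the device, borderline cases may be graded more favourably in the filtration arm. The trial could then report less PGD although the grafts behave the same. Labelling the groups A and B at analysis does not help, because the error is already in the data.

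**Working it through.** **1. When blinding applies and when the end points are measured.**

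| Item | Time | Blinded assessment stated? |
|---|---|---|
| Infiltrates and oedema (end point 2) | days 1-3 | No; image reader not named |
| PGD grade 0-3 (end point 4) | days 1-3 | No; graded in routine care |
| Any PGD (end point 5) | days 1-3 | No; follows from the grade |
| Spirometry, chest CT and kidney function at 1 month | 1 month | Unclear; the rule says after 1 month |
| Later follow-up visits | after 1 month | Yes |
| Statistical analysis | end of study | Yes (groups A and B) |

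What is missing is blinded assessment on days 1-3, not blinded analysis.

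**2. What can be computed without knowledge of the arm.** The chart review already collects blood gases, FiO2 and radiological findings. A program can form PaO2/FiO2 and combine it with the infiltrate finding, which takes discretion out of the grading step. It cannot make the infiltrate finding itself blind. End point 2 is an image reading and cannot be derived from other data.

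**3. The plan's own figure.** The document gives no figure on this point. Its sample size reproduces: with a difference of 60, SD 100, two-sided alpha 0.03 and a two-sample t test, 52 per group gives power 0.803. Adding 10% gives 58 per group, 116 in total. A change in blinding leaves this as it is.

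**4. Illustration of what is at stake.** The document gives no rate for PGD alone (its 40% to 80% covers PGD and CLAD together) and no misgrading rate. Both are therefore assumptions.

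Inputs: true PGD rate p = 0.40 in both arms; n = 58 per arm; a fraction f of true cases in the filtration arm graded as free of PGD; two-sided 5% two-proportion z test.

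Formulas, with q = p(1 − f), d = p − q and p̄ = (p + q)/2:

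- SE under the null: s0 = √[2p̄(1 − p̄)/n]
- SE of the observed difference: s1 = √[(p(1 − p) + q(1 − q))/n]
- Rejection rate = 1 − Φ[(1.96·s0 − d)/s1] + Φ[(−1.96·s0 − d)/s1]

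| f | q | d | s0 | s1 | Upper tail | Lower tail | Rejection rate |
|---|---|---|---|---|---|---|---|
| 0.1 | 0.36 | 0.04 | 0.0901 | 0.0901 | 0.0646 | 0.0081 | 7.3% |
| 0.2 | 0.32 | 0.08 | 0.0891 | 0.0888 | 0.1432 | 0.0021 | 14.5% |
| 0.3 | 0.28 | 0.12 | 0.0880 | 0.0873 | 0.2740 | 0.0004 | 27.4% |

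With 58 per arm and a true rate of 40%, there are 0.40 × 58 = 23.2 true cases in the filtration arm. The three values of f thus mean about 2, 5 and 7 regraded patients.

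**5. Sensitivity.** Exact binomial enumeration with 58 per arm gives 7.0%, 14.2% and 27.4%. With 52 per arm, and true PGD varied from 30% to 50%, it gives 6.5-9.6%, 10.9-19.9% and 18.7-36.9%. With no misgrading, the same enumeration gives 5.1-6.2%.

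**The case against.** The strongest reply is that this is a condensed article. It lists as unblinded only the staff who give the treatment. It does not say that the radiology reader knows the arm, and the full protocol may say who reads the images. This stands in part: the reader's status is unstated, not stated as unblinded. The article does, however, state where blinded assessment begins, and that start falls after the days on which PGD is graded.

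A reader might infer that the early end points have no blinding of any kind. The document does not support that, since the statisticians are blinded and the groups are masked in the analysis.

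A reader might also infer that computing the grade by program makes it fully blind without another reader. It does not. A rule applied to an unblinded image reading stays unblinded in that component. Withholding the allocation from the person who enters the infiltrate item would add little, because that person transcribes a judgement already made. The device is connected for 12 of the first 24 hours, so circumstances on day 1 may disclose the arm. Unblinded staff also influence FiO2 settings and sampling times.

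The figures can be challenged too. The PGD rate and the one-directional misgrading rates are assumed, and at 10% misgrading the inflation is small. The plan analyses repeated measures with mixed models, not a single two-proportion test. All of this stands, so the figures show only the direction and possible scale of the bias. Finally, these are 3 of 14 secondary end points, and an unblinded device trial with routine grading is a familiar limitation. That limits the weight of the point but does not remove it, because PGD is part of the trial's stated purpose.

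**Conclusion.** The concern holds in a limited form. The article states blinded outcome assessment only for visits after 1 month. PGD grade, any PGD and infiltrates on days 1-3 therefore have no stated blinded assessment, and the PGD grade comes from routine care in which treating staff know the allocation. Masked analysis cannot repair that.

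The possible size is known only under assumptions. A few regraded patients in one arm could raise a nominal 5% false-positive rate to somewhere between about 7% and 27%, given a 40% true rate, 58 per arm and errors in one direction only. Nothing in the document shows that such misgrading will occur. The change is worth making because it is cheap and PGD is a headline aim, but the point does not touch the primary end point or the sample size.

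**What to change.** 1. State that the analysed PGD grade on each of days 1-3 is computed by a program from eCRF data. The inputs are the charted PaO2/FiO2 at a fixed time each day and the infiltrate finding in the routine radiology report, graded under the guideline the article already cites. The article gives only the threshold for the presence of PGD, so the derivation must write out the guideline's cut-offs for grades 0-3.
2. Keep the bedside grade as a sensitivity analysis.
3. Leave the allocation off the imaging request, and state who reads the images and whether that reader knows the arm.
4. Extend the existing blinded assessors to the 1-month visit, and word the rule so that this visit is clearly included.
5. State the remaining limit in the trial report: the infiltrate component and end point 2 are blind only if the routine reader does not know the arm, and unblinded staff still influence FiO2 settings.

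The cost is protocol wording, one derivation program and a neutral imaging request. No extra image or additional reader is needed for this reduced aim. The downside is that the derived grade may differ from the bedside grade in some patients, which the sensitivity analysis will show.
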